## Methods

### Overall study design

The study is a randomised controlled trial (RCT) of two active interventions: CFT and PFT. Each participant receives 6 months of treatment and is followed up to 12 months post-treatment completion. Participant flow through the study is shown in Figure 1. Study recruitment began in July 2010 and is estimated to continue until July 2014, with the final 12-month follow-up assessment due to be completed in December 2015. The study is registered with the Australian and New Zealand Clinical Trials Registry (ACTRN 12610000216011). Ethics approval has been granted by the Royal Children’s Hospital Human Research Ethics Committee (#30035).

**Figure 1 F1:**
[figure not shown]
Participant flowchart.

### Setting

The Royal Children’s Hospital Eating Disorder Program is a multidisciplinary specialist program that provides inpatient and outpatient medical management and outpatient FBT for adolescents with AN (see [15] for a detailed program description). The team includes clinicians from the disciplines of paediatrics, psychology, psychiatry, nursing, dietetics, and social work. Patients are referred by their general practitioner or other provider. Following a standardised phone triage conducted with the parents by a clinical nurse consultant, the patient and their parents attend a one-day multidisciplinary assessment clinic for diagnostic evaluation, medical examination and treatment planning. This assessment includes administration of standardised assessments by research staff not involved in treatment delivery. Prior to attending the assessment clinic, families are sent an information pack including written questionnaires.

Patients are also referred for outpatient FBT by the Royal Children’s Hospital adolescent inpatient unit. These patients and their parents undergo the same assessment while an inpatient and commence treatment upon discharge.

### Participants

Participants will be 100 families of adolescents aged between 12 and 18 years inclusive. Eligible participants are identified during triage and intake assessment. Sample size calculation for this study was based upon two controlled trials of FBT [6,8]. It was calculated that for 80% power and a two-tailed significance level of .05, it would be possible to detect an 27% difference between CFT and PFT (dichotomous outcome of remitted versus non-remitted) with a sample size of 45 participants per group. Assuming a dropout rate of 10%, the enrolled sample size requires 50 participants per group.

Treatment groups will be compared on sociodemographic and clinical characteristics at baseline using Fisher’s Exact test for dichotomous variables (e.g., gender, family status), chi-square for categorical variables (e.g., ethnicity, comorbid diagnoses), and independent sample t-tests for continuous measures (e.g., age, % EBW).

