### Data analysis

Remission will be determined separately at post-treatment and follow-up. The primary outcome analysis will be based upon intent-to-treat. In those cases in which there are missing post-treatment or follow-up data, the pre-treatment observation will be carried forward to characterise that participant’s response [58]. Groups will be compared on remission at post-treatment and follow-up using two-tailed Fisher’s Exact test with *alpha* set to .05. The secondary outcome category is the proportion of participants partially remitted. CFT and PFT will be compared at post-treatment and follow-up using Fisher’s Exact test.

A secondary analysis will be performed using a mixed effects linear regression model [59] to compare CFT and PFT participants on eating pathology, depression and self-esteem at mid-treatment (week 12), end-of-treatment (week 24), 6-month follow-up, and 12-month follow-up controlling for pre-treatment levels. Analyses will be performed on log-transformed variables for behavioural frequencies to satisfy the assumptions for the linear model. Random regression models allow for the inclusion of individuals with missing data. Consequently, no data imputation will be performed. Comparisons between groups will be based upon the main effect for group with a two-tailed alpha of .05. *Post hoc* comparisons between groups at specific time-points will be based upon a two-tailed Bonferroni corrected *Post hoc* comparisons between groups at specific time-points will be based upon a two-tailed Bonferroni corrected *alpha* of .0125 (.05/4).

Moderation analyses will be performed using logistic regression analyses, with models using main effects for treatment, moderator, and treatment-by-moderator analyses to predict remission at post-treatment and follow-up assessments. Bootstrap mediation analyses with bias-corrected confidence intervals will be performed using the *PROCESS* macro developed by Hayes [60].

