## Discussion

This trial will be the largest randomised trial of a separated model of FBT for adolescents with AN to date. If found to be efficacious, PFT has the potential to increase recovery rates by offering clinicians and families an alternative approach to standard conjoint FBT.

Although standard FBT has the most promising evidence-base for treatment of adolescent AN [61,62], it has significant limitations. As described earlier, the standard conjoint format described in the manual (i.e., CFT) [9] raises many challenges and is difficult for many families and therapists to adhere to for a variety of reasons [12,19]. Moreover, studies using strict outcome criteria suggest CFT only achieves remission in around 50% of adolescents [6,8]. As individual therapies are generally found to be less effective in this population [8,63], clinicians and researchers tend to focus on improving outcomes by modifying FBT. This trial builds on two previous studies that indicated restructuring FBT with parents and adolescents attending separate sessions may be an efficacious alternative treatment for some families.

Of importance, the trial will not only indicate whether PFT is a more efficacious alternative to CFT, but moderator analyses will indicate whether there are specific patient or family characteristic that are useful in guiding the selection of treatment approach. For example, previous research suggests highly critical families may be better suited to SFT rather than CFT [5,6] and that adolescents with high eating-related obessionality are better suited to CFT than adolescent-focused therapy [64]. Furthermore, mediation analyses in this trial will indicate potential mechanisms of action which could be the target of future efforts to enhance FBT. For example, if remission is shown to be mediated by improved parent efficacy, techniques could be integrated into FBT to increase efficacy in parents who struggle with this during treatment.

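### The stated 80% power fits a large-sample formula, not the planned Fisher's Exact test with baseline carried forward, which gives about 64–75% for a 27-point difference

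*Protocol article*

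**What the plan says.** The Participants section of the protocol article sets the sample size "for 80% power and a two-tailed significance level of .05". It says that "it would be possible to detect an 27% difference between CFT and PFT" in the proportion remitted "with a sample size of 45 participants per group". It then adds: "Assuming a dropout rate of 10%, the enrolled sample size requires 50 participants per group". It gives no assumed remission rate in either arm and names no test for the calculation. It says only: "Sample size calculation for this study was based upon two controlled trials of FBT [6,8"].

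The Discussion, citing the same two references, says that "studies using strict outcome criteria suggest CFT only achieves remission in around 50% of adolescents".

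The Data analysis section fixes the primary comparison: "Groups will be compared on remission at post-treatment and follow-up using two-tailed Fisher’s Exact test", at a 5% level and by intent-to-treat. Where post-treatment or follow-up data are missing, "the pre-treatment observation will be carried forward to characterise that participant’s response".

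Two other sections settle what that rule does. Under Inclusion criteria, entry weight is at most 90% of expected body weight, or at most 95% for adolescents at or above the 75th height percentile. Under Primary outcome, remission needs at least 95% of expected body weight together with an Eating Disorder Examination global score within one standard deviation of community norms.

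**The concern.** The stated power and the stated analysis do not belong to the same design, in two respects.

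- **Test.** Fisher's Exact test is conservative at this sample size. A number taken from a large-sample formula without continuity correction will not give the stated power when Fisher's test is used.
- **Dropout.** Dividing 45 by 0.9 is right if dropouts leave the analysis and 45 per arm remain. Under the stated rule, participants with missing outcomes stay in the denominator with their baseline value, which in practice is non-remitted. That shrinks the expected difference between arms, and raising 45 to 50 does not make up for it.

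This is the primary comparison, and the first hypothesis is that parent-focused treatment (PFT) is superior. If power is about 64–75%, the chance of missing a true 27-point benefit is about 25–36%, against the 20% implied. A non-significant result would then be read against more power than the design has.

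**Working it through.** **Inputs.** Two-sided alpha 0.05, power 80%, difference 27 points (read as absolute), 45 per arm, 10% dropout and 50 enrolled per arm are from Participants. The CFT rate of about 50% is from the Discussion. The Fisher test, intent-to-treat set and baseline carried forward are from Data analysis. The working scenario is therefore 50% v 77%.

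**1. Reproducing the plan's figure.** Unpooled formula: n = (z₀.₉₇₅ + z₀.₈₀)² × [p₁(1−p₁) + p₂(1−p₂)] / d².

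- (1.960 + 0.842)² = 7.849
- 0.50×0.50 + 0.77×0.23 = 0.4271
- d² = 0.27² = 0.0729
- n = 7.849 × 0.4271 / 0.0729 = 46.0 per arm

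Power at 45 per arm: SE = √(0.4271/45) = 0.0974; 0.27/0.0974 − 1.960 = 0.811; power 79.1%. The stated figure is thus reproduced to within one participant per arm. Dropout inflation: 45/0.9 = 50. The pooled-variance version gives 49 per arm, and the continuity-corrected version 56.

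**2. Power of the planned test.** This was found by enumerating every pair of binomial outcomes and adding the probabilities of those with two-sided Fisher p ≤ 0.05.

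| Scenario | Rates | n per arm | Fisher power |
|---|---|---|---|
| 45 analysed, dropouts leave the analysis | 50% v 77% | 45 | 70.8% |
| All 50 analysed, 27 points already the intent-to-treat difference | 50% v 77% | 50 | 75.3% |
| All 50 analysed, 10% per arm missing and scored non-remitted | 45% v 69.3% | 50 | 63.8% |

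The third row multiplies both rates by 0.9: 0.9×50 = 45.0 and 0.9×77 = 69.3, so the difference falls to 0.9×27 = 24.3 points.

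**3. Sensitivity to the CFT rate.** With 45 per arm and a 27-point difference:

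| CFT rate | Fisher power, 45 per arm | Fisher power, 50 per arm with 10% scored non-remitted |
|---|---|---|
| 40% | 65.0% | 63.6% |
| 47% | 68.6% | 63.6% |
| 50% | 70.8% | 63.8% |
| 55% | 74.0% | 64.5% |
| 60% | 78.2% | 66.7% |

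At 45 per arm, Fisher power is below 80% for every CFT rate from 12% to about 61%. It passes 80% only at about 11% or lower, or about 62% or higher.

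**4. What would give 80%.** With 50 per arm and CFT at 50%, the detectable difference is about 28–29 points with no missing data and about 32 points with 10% per arm scored non-remitted. For 27 points, Fisher's test needs 56 analysed per arm, or 72 per arm when 10% are scored non-remitted.

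**The case against.** The strongest reply is that 45 per arm is an ordinary large-sample result. That stands. A reader who tries the pooled formula gets 49 and might infer an arithmetic slip. The article does not support that: it names no formula, the unpooled one gives 46, and the Discussion's rate is only approximate. The fault is a mismatch between calculation and analysis.

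Second, the 50% is inferred. It is a rounded figure in the Discussion, not declared as the planning rate, and a condensed article may leave that rate to the full protocol. This is fair, so the omission is not itself held against the plan. But the figure cites the same two references as the sample-size paragraph, and the shortfall at 45 per arm holds over the whole range from 12% to about 61%.

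Third, a reader might infer that power is simply 64%. The article does not support that either. The figure needs the 27 points to apply to participants with observed outcomes, and every dropout to have missing data. The paragraph says neither. Assessments are part of routine care, so a family that leaves treatment may still be assessed. If 27 points is already the intent-to-treat difference, all 50 per arm give 75%.

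Fourth, Fisher's test is valid and prespecified, and neither feature inflates the type I error. This also stands: keeping the test is legitimate. It is the stated power that does not go with it.

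**Conclusion.** The point holds as a mismatch. The stated 80% power for 27 points does not describe the analysis that the article plans. At a CFT rate of about 50%, the planned Fisher's Exact test has about 71% power with 45 per arm. With 50 per arm it has about 64–75%, depending on how many outcomes are missing and on whether the 27 points is meant before or after missing outcomes are counted as non-remitted.

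The assumptions are a CFT rate near 50%, an absolute difference of 27 points and, for the lower end, 10% missing outcomes in each arm. The direction is robust: even the most favourable of these scenarios falls about 5 points short of 80%.

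**What to change.** Restate the sample-size paragraph for the planned test and missing-data rule. For example: *With 50 participants per arm and an assumed CFT remission rate of 50%, a two-sided Fisher's Exact test at the 5% level has about 75% power for a 27-point difference if no outcomes are missing, and about 64% if 10% per arm are missing and counted as non-remitted. The difference detectable with 80% power is about 28–29 points and about 32 points respectively.* Drop the inflation from 45 to 50 as the allowance for dropout, or say which dropouts it covers. If the planning rate was not 50%, recompute with the rate that was used.

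The cost is one reworded paragraph and a less favourable stated power. No extra patients are needed.

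Optionally, an unconditional exact test (Boschloo) at the same alpha would recover about 5 points of power: 81% v 75% with no missing data, and 69% v 64% with 10% missing. That is a choice of method, not a correction, and it does not restore 80% in the second case.

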### Inclusion criteria

Participants are eligible to participate if they are aged between 12 to 18 years, meet DSM-IV criteria for AN (excluding the amenorrhea criterion) or EDNOS-AN [16], are sufficiently medically stable for outpatient treatment, and are living with at least one parent or guardian who can read and speak English to at least a sixth-grade level. DSM-IV criteria were applied as the trial commenced prior to publication of the DSM-5 [1]. In anticipation of the DSM-5 criteria, however, the amenorrhea criterion was excluded and, in the absence of explicit acknowledgement of fear of weight gain or becoming fat, persistent behaviours that interfere with weight gain are considered diagnostic. Weight thresholds are ≤85% EBW for AN and 85-90% EBW for EDNOS-AN. For adolescents at or above the 75^th^ percentile for height, the weight threshold was set higher (≤95% EBW). EBW is calculated from median body mass index for age and gender using the Centers for Disease Control charts [17]. Medical stability is determined by a paediatrician or nurse according to a standard protocol that was informed by published guidelines [18].

### Exclusion criteria

Participants are excluded from entry into the study if they present with current psychotic disorder, dependence on drugs or alcohol, explicit suicidal risk (i.e., requiring hospitalisation or high level supervision), or a physical condition known to influence eating or weight (e.g., pregnancy, cancer). Participants who have previously received 10 or more FBT sessions with a trained FBT clinician are also excluded. Participants on psychotropic medication who meet inclusion criteria for the study are only eligible for participation if they have been on a stable dose of for a period of at least 8 weeks and the medication has not been prescribed for the primary purpose of weight gain. In the case of patients with current or a history of recent or past physical or sexual abuse by a family member, the perpetrator of the abuse is excluded from treatment. If physical or sexual abuse by a family member occurs in the course of treatment, the perpetrator is excluded from ongoing treatment and appropriate protective services are notified if indicated by Victorian laws.

### Recruitment

Information statements about the RCT are included in the information pack posted to each family prior to attending the assessment clinic. Following completion of the intake assessment and feedback regarding diagnosis, a researcher explains the treatment to the parents and patient and, if eligible, informs them of the RCT and invites them to participate. If the family agrees, the adolescent and parents sign written consent forms. Consent includes a choice of whether to have assessment and treatment sessions audio recorded and whether to allow data to be used for other future ethically-approved research.

### Randomisation

A statistician independent of the research group generated a randomisation schedule using block randomisation with variable block sizes (currently masked from research personnel). Randomisation is stratified by eating disorder severity (low vs. high) to ensure equal allocation to each of the treatment arms. High severity is defined as <80% EBW, illness duration >12 months, and the presence of one other psychiatric diagnosis (i.e., all three criteria must be met). The randomisation schedule is only accessible by designated staff members at the Royal Children’s Hospital who are independent of the Eating Disorders Program team including the research team. When randomisation is required, a researcher sends an email with the participant identification number and severity category to one of the independent staff members requesting randomisation. The allocation is sent via reply email and the researcher communicates the allocation to the family and treating clinicians.

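### The primary Fisher test ignores the severity stratum and the baseline values of both remission components: valid, but inefficient, mainly because Fisher's test is conservative

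*Protocol article*

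**What the plan says.** The Randomisation section of the protocol article states: "Randomisation is stratified by eating disorder severity (low vs. high) to ensure equal allocation to each of the treatment arms". The upper stratum is narrow: "High severity is defined as <80% EBW, illness duration >12 months, and the presence of one other psychiatric diagnosis", and all three conditions must hold together. The share of patients expected in it is not given.

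The Data analysis section fixes the primary comparison: "Groups will be compared on remission at post-treatment and follow-up using two-tailed Fisher’s Exact test with *alpha* set to .05". Partial remission gets the same test. Neither comparison includes the stratum or a baseline covariate. In the same section, the mixed models for the continuous secondary outcomes do adjust for pre-treatment values, and logistic regression is planned for moderation only.

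Full remission combines %EBW of at least 95 with an EDE Global score near community norms (Primary outcome). Table 1 shows that weight, height and the EDE are all collected at baseline.

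**The concern.** Stratifying on severity presumes that severity predicts outcome, and the third hypothesis expects psychiatric comorbidity, one of the three stratum criteria, to worsen it. An analysis that drops the stratum does not follow the design. It also leaves unused the baseline values of the two quantities that define remission. Because the high stratum is probably small, stratification gives limited protection against chance differences between arms in weight or symptoms, and the primary test has no means of taking such differences into account.

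What is at stake is precision in the comparison that decides the trial, at a sample size with no margin. The test is written into the article explicitly, so this is a stated choice and not a detail left to an analysis plan.

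**Working it through.** **Inputs.** The Participants section gives a 27% difference (read as percentage points), 80% power, two-sided .05, 45 per group, and 50 per group after 10% dropout. The Discussion puts CFT remission at around 50%; the sample size paragraph names no control rate. Data analysis carries the pre-treatment observation forward when data are missing. Entry weight is capped, so I count all dropouts as non-remitted.

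**The plan's own figure.** With unpooled variance and no continuity correction, n = (1.960 + 0.842)² × (0.50×0.50 + 0.77×0.23) / 0.27² = 7.849 × 0.4271 / 0.0729 = 45.98. That is 46, close to the stated 45 (power at 45 is 79.1%), and 45/0.9 = 50. The figure therefore reproduces, but under a normal approximation and not under the planned test.

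**Power of the planned test.** Exact enumeration: sum, over all pairs of remission counts (i, j), Bin(i; n, p₁) × Bin(j; n, p₂) wherever the two-sided Fisher p-value is at most .05.
- 50% v 77%, 45 per arm: 70.8%.
- 50% v 77%, 50 per arm, all observed: 75.3%.
- Carry-forward with 10% dropout: 0.9 × 50% = 45% v 0.9 × 77% = 69.3%, 50 per arm: 63.8%.
- Equal rates of 30% to 60%, 50 per arm: true size 3.1% to 3.5%.

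**Where the power goes** (45% v 69.3%, 50 per arm). The chi-square figure is exact. The logistic figures are simulated likelihood-ratio tests with two standard-normal baseline covariates.

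| Analysis | Power |
|---|---|
| Fisher | 63.8% |
| Unadjusted chi-square | 71.2% |
| Logistic, two useless covariates | about 70–73% |
| Logistic, OR about 1.5 per SD each (log-OR 0.4) | about 73% |
| Logistic, OR about 2.0 per SD each (log-OR 0.7) | about 77% |

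Leaving Fisher's test gives 71.2 − 63.8 = 7.4 points. Baseline information adds 73 − 71.2 = about 2 to 77 − 71.2 = about 6 points.

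**The stratum alone.** This was simulated separately with stratified 1:1 allocation, 3,000 trials per scenario, an assumed high-stratum share of 5–30% and an assumed stratum odds ratio of 1–5. Compared with the unadjusted chi-square, a Cochran-Mantel-Haenszel test by severity changed power by about −1 to +3 points. For example, at 45% v 69.3%, with a 10% share and an odds ratio of 3, chi-square had 73.1% and Cochran-Mantel-Haenszel 72.7%. The largest gain (79.7% to 82.5%) was at 50% v 77% with 45 per arm, a 30% share and an odds ratio of 5.

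The share may be lower still. If the three criteria were independent, with assumed prevalences of 30–40%, 25–35% and 40–60%, it would be 0.30×0.25×0.40 = 3% to 0.40×0.35×0.60 = 8.4%.

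**Everything together.** In the same simulations at 45% v 69.3%, Fisher had 63–68%, Cochran-Mantel-Haenszel 69–75%, and logistic regression with the stratum plus one baseline score (assumed odds ratio 1–2.5 per SD) 72–79%.

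**Type I error.** Fisher was at 1.5–2.9% in the stratified simulations at 45 per arm. Adjusted logistic regression was around 5%, with single scenarios between 4.9% and 6.4%.

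**The case against.** The strongest reply is that nothing here is invalid. Randomisation makes the unadjusted comparison valid, chance imbalance is already covered by the nominal error rate, and ignoring a stratification factor makes the test conservative. Fisher's test also guarantees a type I error of at most 5% without a model, and the adjusted test does not. This stands. A reader might infer from the mismatch between design and analysis that the result will be biased; the documents do not support that.

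A reader might also infer that ignoring the stratum is the main cause of the lost power. It is not. Even useless covariates bring logistic regression to about the power of the plain chi-square, and the stratum by itself moves power very little. If the stratum is as small as its definition suggests, adjusting for it can recover little and may cause separation.

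The prognostic strength of baseline %EBW and EDE Global is an assumption. The article quantifies neither and does not list them among its predictors, and the entry criteria narrow the range of baseline weight. This also stands, and is why the adjustment gain is given as a range.

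Finally, the gap between the claimed 80% and the power of Fisher's test is a sample size question. It depends on the control rate: at the earlier trial's 47% v 76%, Fisher has 76% with 45 per arm. It is the background to this point and should not be counted twice.

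**Conclusion.** The point holds as one of efficiency. At the article's own effect and its cited CFT rate, with 10% dropouts counted as non-remitted, the planned test has about 64% power. A prespecified baseline-adjusted analysis would have about 73–77% if both baseline covariates carry an odds ratio of 1.5–2.0 per SD. Most of that difference, about 7 points, comes from replacing a test whose true size is 3.1–3.5%. Baseline adjustment contributes about 2–6 points under the assumed strengths, and the severity stratum alone about −1 to +3.

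The case for including the stratum is therefore mainly consistency with the randomisation. Including the baseline components adds modest precision and takes chance imbalance in them into account. A reader might hope that adjustment rescues the planned 80%; under the carry-forward rule it does not do so reliably. The change is worth making because it is cheap, and it needs to be fixed before results are seen.

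**What to change.** Prespecify as the primary analysis a logistic regression of remission on arm, adjusted for severity stratum, baseline %EBW and baseline EDE Global, with penalised likelihood if the small stratum causes separation. Report the standardised risk difference with its 95% CI. Analyse partial remission in the same way. Keep the two-tailed Fisher's exact test as a supporting analysis.

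The cost is wording only, since every covariate is already collected at baseline. The price in inference is that Fisher's guaranteed error bound is exchanged for approximate control, around 5% in simulation and slightly above it in some scenarios. The plan should say so, and should not present the change as restoring the stated power.
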